#### Randomization

Patients will be randomized 1:1 to control or intervention. Randomization will be done centrally by computer-generated random numbers, and a secure internet-based allocation method that ensures allocation concealment from all research personnel; randomization will be stratified by participating SPC. As this study is unblinded, variable sized blocked randomization will also be used to preserve allocation concealment. Because our intervention is distinct from usual care and current standards of care in participating clinics are well demarcated, the risk of contamination (by altering the practices of physicians in participating SPCs) is low. Furthermore, our pilot data suggests that the ratio of patients enrolled to primary care physicians affected in this study is essentially 1:1--that is, it is unlikely that any one of the almost 950 primary care physicians in Edmonton will have more than one patient enrolled in this study. Thus, the patient will be the unit of randomization and analysis in this study.

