#### Outcomes

Because this is an active control trial, we expect improvements in all aspects of care in the control arm--due to both active intervention by stroke specialists within the SPCs and the referring primary care physicians in response to the monthly reminders about each study participant's BP, various secular/temporal influences as they relate to vascular risk reduction, study volunteer and Hawthorne effects, and regression to the mean. The importance of a control group cannot be over-emphasized. For example, in the ESP-CAD trial, we found a 50% absolute improvement in statin management in the control group [35]. Therefore, all continuous measurements will be 'changes' from baseline to six months, comparing the changes achieved in the intervention group with those in the control group.

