#### Sample size

In a survey of members of the divisions of neurology and general internal medicine at the University of Alberta, we determined that the 'minimal' clinically important difference for this particular intervention to be considered useful was a 10% absolute improvement in the proportion of patients achieving 'optimal BP and lipid control' over and above usual care. After six months, we estimate that no more than 5% of control patients will have attained our composite primary outcome (given that patients who are at goal BP and lipid levels at baseline will be excluded from this study). We calculated our sample size to detect a 10% absolute increase in the primary outcome, set the alpha error rate at 0.05 (2-sided), and the beta error at 0.20 (power 80%); this yielded a minimal necessary sample size of 140 patients per study arm.

The calculated sample size will also provide 80% power (assuming a standard deviation of 15 mm Hg, as recently found in our trial of diabetic hypertensive patients) [34] to detect a 5 mm Hg between-group difference in systolic BP at six months with alpha of 5% for a two-sided test. Based on a review of the literature, consensus of the investigators, and consensus of over two dozen members of the Evidence-Based Recommendations Task Force of the Canadian Hypertension Education Program (surveyed by [name], in his role as Chair of the Central Review Committee for the Evidence-Based Recommendations Task Force of the Canadian Hypertension Education Program]), a 5 mmHg sustained difference in SBP, over and above usual care, would be considered clinically meaningful.

A sample size of 140 patients per group will also provide 85% power (assuming a standard deviation of 0.84 mmol/L, as recently found in our trial in patients with coronary disease) [35] to detect a 0.3 mmol/L between-group difference in fasting LDL cholesterol at six months with alpha of 5% for a two-sided test. This sample size will also provide 85% power (assuming a standard deviation of 14%, as recently found in a trial of 2,687 patients) [53] to detect a 5% between-group difference in projected five-year risk of cardiovascular disease at six months with alpha of 5% for a two-sided test.

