### Statistical analysis

All sociodemographic and clinical characteristics at baseline and follow-up will be summarized using percentages for categorical variables and medians (interquartile range) for continuous variables. Chi square tests will be used to compare the proportion of patients who attain 'optimal BP and lipid control' at six months (because the proportion at baseline will be zero by definition), as well as other binary secondary outcomes such as proportions that achieve target BP and lipid levels. Patient and health system factors associated with meeting BP and lipid goals will be assessed in multivariate analyses. To compare changes in systolic BP, LDL cholesterol, and total:HDL cholesterol ratios between intervention and control, we will use 2-sample independent t-tests. In the event that any baseline characteristics are not balanced between study groups, we will employ multivariate extensions of our primary analytic plan (*i.e*., substituting multiple linear regression for t-test or multiple logistic regression for Chi square test), adjusting for any clinically important (*i.e*., greater than 10% imbalance between arms) or statistically significant (*i.e*., p-value of < 0.10 between arms) differences observed between groups.

All analyses will be by intention to treat. Missing data at the six-month follow-up assessment will be imputed with a 'baseline-observation carried forward' strategy; this approach conservatively assumes that all subjects lost to follow-up have had no change in their BP or lipid levels. As a sensitivity analysis for this assumption, we will also analyze the data in an 'on-treatment' analysis, using only those cases with complete follow-up data for each analysis.

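### Changes in SBP, LDL and lipid ratio are compared by unadjusted t-tests; prespecified baseline-adjusted ANCOVA would be more precise

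*Protocol article*

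**What the plan says.** The Outcomes section of the protocol article puts every continuous outcome on the change scale: "all continuous measurements will be 'changes' from baseline to six months, comparing the changes achieved in the intervention group with those in the control group". The Statistical analysis section then names the test: "To compare changes in systolic BP, LDL cholesterol, and total:HDL cholesterol ratios between intervention and control, we will use 2-sample independent t-tests".

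Adjustment is conditional: "In the event that any baseline characteristics are not balanced between study groups, we will employ multivariate extensions of our primary analytic plan". For continuous outcomes this means that multiple linear regression takes the place of the t-test. The triggers are "greater than 10% imbalance between arms) or statistically significant", the latter defined as p<0.10 between arms.

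The Sample size section gives two secondary power statements for 140 per arm at two-sided 5%. One is 80% power, with an SD of 15 mm Hg, "to detect a 5 mm Hg between-group difference in systolic BP at six months". The other is 85% power for 0.3 mmol/L in LDL with an SD of 0.84 mmol/L. Neither says whether the SD belongs to the six-month value or to the change, and no baseline to follow-up correlation is given.

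**The concern.** Patients enter because SBP, LDL or the lipid ratio is raised, and the Outcomes section itself expects regression to the mean. In that setting the slope of the six-month value on baseline is below 1. A change score subtracts the whole baseline value, as if the slope were 1, and so adds avoidable noise. A chance baseline difference between arms then carries into the comparison, in the opposite direction.

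The conditional regression does not remove this. It depends on what is observed at baseline, so the model is chosen from the data. Moderate gaps stay below the threshold, and the rule does not single out the outcome's own baseline as a covariate. At stake are precision and power on the main continuous secondary outcomes.

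**Working it through.** **Inputs.** From Sample size: n = 140 per arm; SBP difference 5 mm Hg, SD 15; LDL difference 0.3 mmol/L, SD 0.84; two-sided alpha 0.05. From Randomization: "Patients will be randomized 1:1 to control or intervention". Assumed, because the article does not give them: r from 0.3 to 0.7, and equal baseline and six-month SDs.

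**1. The stated powers reproduce.** Power = Φ(δ / (SD·√(2/n)) − 1.96).

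- SBP: 15 × √(2/140) = 1.793; 5/1.793 = 2.789; Φ(0.829) = 79.6% (stated 80%).
- LDL: 0.84 × √(2/140) = 0.1004; 0.3/0.1004 = 2.988; Φ(1.028) = 84.8% (stated 85%).

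The noncentral t gives 79.4% and 84.6%.

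**2. Relative precision.** With a common SD s:

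- variance of change = 2s²(1−r)
- ANCOVA residual variance = s²(1−r²)
- ratio ANCOVA/change = (1+r)/2, which is 0.65, 0.75 and 0.85 at r = 0.3, 0.5 and 0.7.

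Without the equal-SD assumption, the change-score variance exceeds the ANCOVA variance by s0²(1−b)², where s0 is the baseline SD and b the slope on baseline. The excess is zero only if b = 1. If selection at entry narrows s0, the size of the gain alters, but in large samples ANCOVA is never the less precise method.

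**3. Power if the stated SD is the SD of change.** The t-test keeps 79.6% (SBP) and 84.8% (LDL) at every r. The ANCOVA SD is SD·√((1+r)/2).

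| r | ANCOVA SD, SBP | ANCOVA power, SBP | ANCOVA power, LDL |
|---|---|---|---|
| 0.3 | 12.09 | 93% | 96% |
| 0.5 | 12.99 | 90% | 93% |
| 0.7 | 13.83 | 86% | 90% |

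**4. Power if the stated SD is that of the six-month value.** The change SD is s√(2(1−r)) and the ANCOVA SD is s√(1−r²).

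| r | Change SD, SBP | t-test, SBP | ANCOVA, SBP | t-test, LDL | ANCOVA, LDL |
|---|---|---|---|---|---|
| 0.3 | 17.75 | 65% | 83% | 71% | 88% |
| 0.5 | 15.00 | 80% | 90% | 85% | 93% |
| 0.7 | 11.62 | 95% | 97% | 97% | 99% |

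**5. What the imbalance rule lets through.** Assume a baseline SBP SD of 15. Reaching p<0.10 with 140 per arm needs a gap of about 1.645 × 1.793 = 2.9 mm Hg. At an assumed slope of 0.5, a gap of that size moves the change-score contrast by 0.5 × 2.9 ≈ 1.5 mm Hg, about 30% of the 5 mm Hg that the article calls clinically meaningful. If the 10% trigger is read as 10% of a mean near 140 mm Hg (an assumption), it requires 14 mm Hg.

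**The case against.** A t-test on change is a valid, prespecified analysis. Under 1:1 randomisation regression to the mean acts equally on both arms in expectation, and the Outcomes section cites it as a reason for having a control group. A reader might infer that the planned test is biased. It is not: the issue is precision, and the effect of a chance imbalance in the one trial that is run. This objection stands.

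A reader might also infer that the stated 80% and 85% are wrong, or that they hinge on an undisclosed correlation. The documents do not support that. Both figures reproduce, and they depend on r only if the SDs are those of the six-month value. The wording of the power statements leans towards that reading. The Outcomes section, and the planned interim check of assumptions about changes and their SDs, lean towards an SD of change. The figures come from earlier trials that are not at hand, so the question stays open. The 65% for SBP needs both the six-month reading and r = 0.3.

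The plan does contain an adjustment rule, and it would be wrong to describe the analysis as never adjusted. The rule is only a partial answer, because it acts on observed imbalance and does not guarantee the covariate that matters most.

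Finally, the variance ratio could be read as 15% to 35% fewer patients. The trial would not shrink: the binary primary outcome fixed the 140 per arm.

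**Conclusion.** The point holds as one of efficiency on secondary outcomes. The default analysis of SBP, LDL and the total:HDL ratio discards precision that already collected baseline data would provide, and the imbalance-triggered regression does not reliably recover it. ANCOVA needs 65% to 85% of the change-score variance, given equal SDs and an assumed r of 0.3 to 0.7. Its power advantage for SBP is about 6 to 14 percentage points if 15 mm Hg is the SD of change, and about 2 to 18 points if it is the SD of the six-month value. The direction of the gain does not depend on which reading is right; its size does.

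There is no arithmetical error in the power statements, no bias in the planned test, and no effect on the primary chi-square comparison or the sample size. That the type of SD is not stated is a minor lack of clarity. It has some practical weight, because the monitoring board is to compare the assumed SDs with the data and may advise enlarging the trial or ending it for futility.

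**What to change.** In the Statistical analysis section, replace the t-tests and the imbalance-triggered adjustment, for these three outcomes, with one unconditional model each: the six-month SBP, LDL or total:HDL ratio regressed on arm, its own baseline value and stroke prevention clinic (the randomisation stratum). If the effect is still to be described as a difference in change, the wording can stay: with baseline in the model, the arm coefficient is the same whether the response is the six-month value or the change.

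In the Sample size section, state whether 15 mm Hg and 0.84 mmol/L are SDs of the six-month value or of the change, and give the assumed correlation if they are the former.

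The cost is wording only. Baseline BP and laboratory values are already collected, and no visit, measurement or patient is added.

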### Study setting

All three SPCs in Edmonton, Canada (population 1.1 million people) are participating in this trial.

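### The primary chi-square test is replaced by a logistic model whose covariates are chosen by chance baseline imbalance, and neither version plans for the clinic stratification factor

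*Protocol article*

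**What the plan says.** All of the analysis text is in the protocol's Statistical analysis section. For the primary outcome, "Chi square tests will be used to compare the proportion of patients who attain" optimal blood pressure and lipid control at six months. The same section then makes that choice conditional: "In the event that any baseline characteristics are not balanced between study groups, we will employ multivariate extensions of our primary analytic plan". It explains the extension as "substituting multiple linear regression for t-test or multiple logistic regression for Chi square test", so the adjusted model takes the place of the named test and is not an additional analysis. The covariates are the variables that meet either of two criteria: "greater than 10% imbalance between arms" or "p-value of < 0.10 between arms". The variables to be screened are not listed, and the text does not say whether 10% is absolute or relative.

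Under Randomization, "Patients will be randomized 1:1 to control or intervention" and "randomization will be stratified by participating SPC". Study setting gives the number of strata: "All three SPCs in Edmonton, Canada (population 1.1 million people) are participating in this trial". Neither the chi-square test nor the regression that replaces it is said to include SPC.

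**The concern.** In a properly randomised trial, baseline differences between arms arise by chance. A significance test on them shows nothing about whether a variable predicts the outcome. A rule that adjusts for whatever happens to differ can bring in irrelevant variables and leave out important ones. Here the obvious predictors are baseline systolic pressure and baseline LDL. Patients qualify on pressure, LDL or the cholesterol ratio, so they start at different distances from the two targets that make up the composite. Yet these two variables enter the model only if they happen to be imbalanced. SPC would almost never enter, because blocked randomisation within clinic keeps it balanced.

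Two things are at stake. The first is clarity: until baseline data are in, nobody knows which model is primary or what it contains, and with no variable list and an ambiguous 10%, two careful analysts could build different primary models. The second is efficiency: information known at the design stage goes unused.

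**Working it through.** **1. Which test the sample size assumes.** Inputs from Sample size: 5% versus 15%, two-sided alpha 0.05, power 80%, stated n = 140 per arm. With pooled variance under the null and mean proportion 0.10:

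n = [1.960 × √(2 × 0.10 × 0.90) + 0.842 × √(0.05 × 0.95 + 0.15 × 0.85)]² / 0.10² = (0.8315 + 0.3521)² / 0.01 = 140.1, or 141 rounded up.

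Power at 140 per arm is 80.0%. The stated figure reproduces as that of an unadjusted, unstratified comparison of two proportions.

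**2. How often the p < 0.10 criterion fires.** For k independent baseline variables under correct randomisation, P(at least one) = 1 − 0.9^k. The protocol does not give k, so a range is shown.

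| k (assumed) | P(at least one p < 0.10) |
|---|---|
| 5 | 41% |
| 10 | 65% |
| 15 | 79% |
| 20 | 88% |
| 30 | 96% |

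Correlation between variables would lower these figures; the separate 10% criterion would raise them.

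**3. The 10% criterion.** For a binary variable of prevalence p with 140 per arm, the standard error of the difference is √(2p(1 − p)/140).

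- Read as absolute, at p = 0.5: SE = 0.0598, 0.10/0.0598 = 1.67, two-sided probability 9.4%. At p = 0.10 it is 0.5%; at p = 0.74 (the hypertension prevalence in the pilot data) it is 5.6%.
- Read as relative: 78% at p = 0.10, 40% at p = 0.5 and 16% at p = 0.74.

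The two readings give very different covariate lists.

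**4. What the rule does to the result.** Simulation with 140 per arm and 4,000 replicates per scenario. Assumed, because the protocol gives none of it: three clinics of 120, 80 and 80 patients with 1:1 allocation within clinic; 15 independent normal covariates, of which three are prognostic, with a log odds ratio of 0.4 (modest) or 0.8 (strong) per SD. The rule adjusts for every covariate with p < 0.10 and otherwise uses the chi-square test; the 10% criterion was not simulated. The fixed model always contains the three prognostic covariates.

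Power at 5% versus 15%:

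| Scenario | Chi-square | Rule | Fixed model | Rule and chi-square disagree |
|---|---|---|---|---|
| Modest predictors | 81.5% | 80.4% | 82.3% | 4.6% |
| Strong predictors | 80.9% | 79.9% | 85.6% | 5.3% |
| Modest predictors plus clinic effect (log odds −0.7, 0, +0.7) | 79.3% | 77.6% | 79.6% | 4.6% |

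Gain of the fixed model over chi-square: 82.3 − 81.5 = 0.8, 85.6 − 80.9 = 4.7 and 79.6 − 79.3 = 0.3 points. In the clinic-effect scenario, the Cochran-Mantel-Haenszel test by clinic has 80.5% power, a gain of 80.5 − 79.3 = 1.2 points. The Monte Carlo standard error of a single power figure is √(0.8 × 0.2/4,000) = 0.6 points.

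Under the null (5% or 10% in both arms), type I error of the rule was 3.2% to 4.5%. The rule and the chi-square test disagreed in 1.5% to 2.0% of trials. Even reporting whichever of the two was significant gave 4.8% to 5.5%.

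**5. Room for covariates.** Planned events: 140 × 0.05 + 140 × 0.15 = 7 + 21 = 28. A model with arm, two clinic indicators, baseline pressure and baseline LDL has 5 coefficients besides the intercept, or 28/5 = 5.6 events each. A longer list picked by imbalance would be less stable still.

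**The case against.** The strongest defence is that this is a written algorithm with numeric thresholds. It depends only on baseline data, and Outcomes ascertainment says that those analysing the data will be blinded. That stands: it is a poor prespecified rule, not a free choice made after seeing results. An unadjusted chi-square test is also a legitimate primary analysis and matches the sample-size calculation. Leaving a stratification factor out of it does not make it invalid, and the cost here is about one point of power. As this is a condensed article, silence about SPC alone would carry little weight; it counts here because the article does spell out how covariates are chosen, and that method would hardly ever select SPC.

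A reader might infer more than the protocol supports:

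- **That the rule inflates false positives.** The simulation shows no inflation.
- **That a trigger rate of 88% means the conclusion changes that often.** That rate assumes 20 independent variables, and firing is not the same as changing significance, which happened in about 5% of simulated trials at the design effect.
- **That the reported effect becomes a conditional odds ratio.** The Statistical analysis section names tests and models but no effect measure, and a logistic model can yield a risk difference. The protocol leaves the effect measure open; it does not state a wrong one.

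**Conclusion.** The point holds as one that should be fixed, not as a threat to validity. The stated rule lets chance imbalance decide the primary model and its covariates, with no list of variables and an undefined 10%. SPC is planned into neither version. The trigger would fire often, in 41% to 88% of trials for 5 to 20 independent variables on the p-value criterion alone. Its effect on the answer is modest: disagreement on significance in about 5% of trials at 5% versus 15%, and no power gained over the plain chi-square test. Fixed adjustment for prognostic covariates would gain about 0 to 5 points depending on their strength, and SPC alone about 1 point. The trigger rates rest on an assumed number of independent variables. The power figures rest on assumed covariate effects and clinic sizes.

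**What to change.** Remove the imbalance trigger from the primary analysis and prespecify one analysis that applies whatever the balance. The preferred form is a logistic model of attainment on arm, SPC, baseline systolic pressure and baseline LDL, reported as a standardised risk difference with its confidence interval, so that the result is on the same scale as the 10-point absolute difference in Sample size. At minimum, use a Cochran-Mantel-Haenszel test stratified by SPC. Keep the unadjusted chi-square test and any imbalance-driven adjustment as sensitivity analyses; for the latter, list the variables to be screened and say whether 10% is absolute or relative.

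The cost is wording only. SPC, baseline pressure and baseline LDL are already collected, and the 140 per arm need not change. The downside is a few extra parameters with about 28 planned events, so the list should go no further than these three covariates; if that is thought too many, the stratified test is the simpler choice. The change should be made before any outcome data are seen by arm, including at the interim analysis.

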## Background

Epidemiological studies have shown that a number of common conditions increase the risk of stroke and other vascular diseases, and there is compelling evidence from large randomized trials that treatment of such conditions, especially hypertension and high cholesterol, can lead to a significant reduction in the incidence and recurrence of cardiovascular events [1-6]. We know that vascular risk factors, in particular hypertension and high cholesterol, are not managed optimally in patients after stroke or transient ischemic attack (TIA), even in those patients seen in specialized stroke prevention clinics (SPCs) [7,8]. The recent Canadian best practice recommendations for stroke care [9] highlighted this care gap and emphasized that 'new strategies to support clinical practice...are urgently needed'. Implementation of such strategies is important because the risk of recurrent vascular events is high in patients who have suffered a stroke or TIA (*e.g*., in a recent study of 2,285 TIA survivors in Alberta, the rate of stroke, myocardial infarction (MI), or death at one year was 22%) [10]. Stroke prevention strategies need to extend beyond the use of anti-platelet agents, anticoagulation, and carotid endarterectomy, and start addressing the need for more aggressive management of the key stroke risk factors of hypertension and hyperlipidemia, as well as consideration of other modifiable factors such as medication adherence, smoking cessation, diabetes, exercise, and weight loss.

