#### Secondary outcomes

Secondary outcomes will include change in systolic BP at six months versus baseline, proportion achieving BP target (SBP ≤140 mmHg), change in LDL cholesterol at six months versus baseline, proportion attaining LDL cholesterol targets (LDL ≤2.0 mmol/L), proportion attaining total:HDL cholesterol ratios ≤4.0, changes in the cardiovascular disease life expectancy model score [53], changes in other vascular risk factors (waist circumference, body-mass index, self-reported smoking rates, and physical activity), and therapy changes (including number, dosing, and self-reported adherence with antihypertensive and lipid lowering agents). Although differences in clinical events are not anticipated given the short duration of this trial, data will be collected on all-cause hospitalizations, emergency room visits, primary care physician visits, mortality, and clinical events (confirmed by an independent outcome validation committee, blinded to allocation status) such as stroke, TIA, MI, or revascularization. We will also examine humanistic outcomes such as changes in EUROQOL(EQ)-5D [59] and the modified Rankin scale [60] in intervention versus control patients over the course of the trial and will collect direct and indirect costs to conduct a formal cost-effectiveness analysis if the intervention is efficacious. Finally, in order to explore the sustainability of any changes induced by the six-month intervention, we will examine changes in the primary and secondary outcomes at twelve months in both study arms (*i.e*., six months after the intervention stopped). Note that all data will be collected during active follow-up in the twelve-month study period, and further clinical event data will be collected by passive follow-up (for up to five years) through annual linkage to provincial physician billing databases/Canadian Institute for Health Information (CIHI)/provincial vital statistics and registered persons databases after completion of this study as per prior studies by our group [61].

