#### Outcomes ascertainment

The primary and secondary outcomes will be collected and analyzed in an independent and blinded manner by research personnel who have not been involved in the patient's care and will be blinded to patient's randomization group and baseline measurements (including BPs). Thus, although patients and their physicians cannot be masked to the fact that they are in the intervention arm, those collecting outcome data and analyzing the data will be blinded.

Systolic BP will be ascertained at baseline and at six months using the BPTru^® ^device. All study-related lab measurements, collected at baseline, six, and 12 months, will be drawn and independently analyzed at one central lab (Dynalife Dx, Edmonton, Alberta, Canada). All survey instruments will be administered locally at baseline, 6, and 12 months, but collated and analyzed at one central lab, the Epidemiology Coordinating and Research (EPICORE) Centre, Division of Cardiology, University of Alberta. Clinical events reported by patients, their family members, or their primary care physicians will be independently validated by the central outcome validation committee that will be blinded to patients' allocated treatment arms. All patients will be asked to sign the appropriate consent and privacy forms needed to permit examination of clinical outcomes, resource use, and vital status at six months and one year (to cross-check and validate data collected at the active follow-up appointments), and at five and ten years, to gain further insights into long-term clinical event rates.

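### As worded, the six-month baseline-carried-forward rule gives a patient who has died a change of zero on EQ-5D and modified Rankin, and the sensitivity analysis does not correct this

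*Protocol article*

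**What the plan says.** The Statistical analysis section first sets the analysis set: "All analyses will be by intention to treat". It then sets one rule for missing six-month values: "Missing data at the six-month follow-up assessment will be imputed with a 'baseline-observation carried forward' strategy". The reason follows at once: "this approach conservatively assumes that all subjects lost to follow-up have had no change in their BP or lipid levels". Death is not mentioned.

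The only sensitivity analysis of this assumption is a complete-case one, "using only those cases with complete follow-up data for each analysis".

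Under Secondary outcomes, the plan includes "changes in EUROQOL(EQ)-5D [59] and the modified Rankin scale [60] in intervention versus control patients over the course of the trial". Under Outcomes ascertainment, the timing is given: "All survey instruments will be administered locally at baseline, 6, and 12 months". The Outcomes section makes every continuous measure a change from baseline to six months, compared between arms.

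Mortality and adjudicated clinical events are collected as separate secondary outcomes. Patients are also asked to consent to a check of vital status at six months and at one year.

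**The concern.** The rule is general, but its justification is specific. For BP or LDL in a patient who has stopped attending, no change from baseline is an assumption one can argue about. For quality of life or function in a patient known to have died, it is a value that the trial's own vital-status data contradict, and calling it conservative does not apply.

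Intention to treat needs a six-month value for every randomized patient, and the article offers no source for that value other than baseline. A patient who dies in month 3 would therefore be analysed as unchanged in quality of life and function. The complete-case analysis leaves that patient out. One analysis scores the death as neutral and the other ignores it, so agreement between them would say nothing about the effect of deaths on these scales. If the planned cost-effectiveness analysis uses EQ-5D, it would take over the same values.

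**Working it through.** **Inputs from the article.** There are 140 patients per arm (Sample size). That figure reproduces: 5% v 15%, two-sided alpha 0.05 and 80% power give 141 per arm with pooled variance and 138 with unpooled variance, and power at 140 is 80.0%. It serves here only as the denominator. The article gives no figure for deaths, EQ-5D or Rankin scores.

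**Assumed inputs.** Baseline EQ-5D is 0.7 to 0.8 and baseline Rankin is 1 to 2. Death is scored 0 on EQ-5D and 6 on Rankin. Patients who die have the average baseline value.

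**Mean change in one arm.** Let m be the proportion dead by six months, s the mean change in survivors and u the baseline EQ-5D.

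- Baseline carried forward: (1 − m) × s + m × 0
- Complete cases: s
- Death scored 0: (1 − m) × s − m × u

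The third line minus the first is −m × u, whatever survivors do. For Rankin the corresponding term is + m × (6 − b), where b is the baseline score. Carry-forward and complete cases both set this term to zero.

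**Per death in an arm of 140.**

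- Rankin, baseline 1: (6 − 1)/140 = 0.036 points
- EQ-5D, baseline 0.8: 0.8/140 = 0.0057, about 0.006 units

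For a split of 1 v 4 deaths (three extra in one arm), the omitted difference is 3 × 5/140 = 0.107 Rankin points and 3 × 0.8/140 = 0.017 EQ-5D units.

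**Range over assumed six-month mortality.** The omitted between-arm difference is the mortality difference times u, or times (6 − b):

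| Mortality by arm | EQ-5D (u = 0.7 to 0.8) | Rankin (b = 2 to 1) |
|---|---|---|
| equal | 0 | 0 |
| 1% v 3% | 0.014 to 0.016 | 0.08 to 0.10 |
| 2% v 5% | 0.021 to 0.024 | 0.12 to 0.15 |
| 2% v 10% | 0.056 to 0.064 | 0.32 to 0.40 |

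**What the article offers on event rates.** The Background cites Alberta TIA survivors in whom "the rate of stroke, myocardial infarction (MI), or death at one year was 22" per cent. For 280 patients over half a year this is 280 × 0.22 × 0.5 = about 31 composite events, or 280 × (1 − √0.78) = about 33 with a constant hazard. These are not deaths, and the fatal share is not stated. An assumed six-month mortality of 1% to 4% would mean 3 to 11 deaths among 280. For comparison, the 3% loss to follow-up in the group's most recent trial would be about 8 patients of 280. Whether that figure includes deaths is not stated.

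**Primary outcome.** A patient not at both targets at baseline who then dies counts as a non-attainer under carry-forward. Only a patient enrolled on the total:HDL ratio alone could be at both targets at baseline and be carried forward as a success.

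**The case against.** The best defence is that the article never says deaths are to be imputed. The rule covers missing data and its reason speaks of losses to follow-up, so a known death arguably falls outside it. The scoring of deaths on secondary scales is also something a full protocol or analysis plan, not shown here, may settle. This stands in part, because the application to deaths follows from the general wording and not from an explicit statement. It does not remove the point. The article does more than stay silent: it fixes an unqualified rule under intention to treat and gives no other rule for EQ-5D or Rankin.

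A reader might infer more than the document supports:

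- *Arms that differ in mortality would look alike.* They would not. Mortality and clinical events are collected separately, and differences among survivors would still show. Only the death component of EQ-5D and Rankin change is lost.
- *The results would point the wrong way.* Nothing in the document shows this. It states that no difference in clinical events is expected, and it excludes patients with short life expectancy or severe comorbidity. A split of 1 v 4 deaths in 140 per arm is itself compatible with chance (Fisher exact two-sided p = 0.37).
- *QALYs would be wrong.* The article does not mention QALYs. The cost-effectiveness analysis is conditional on efficacy and its method is not given.

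It is also fair to say that scoring death within the scale is one estimand, and that survivors' scores reported beside mortality is another. Either is defensible if stated. Carrying the baseline value through death corresponds to neither.

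**Conclusion.** The point holds as a defect of wording with a limited consequence. The six-month rule is broader than its justification. Applied as written, it assigns two named secondary outcomes a value known to be false for patients who have died, and the complete-case analysis cannot reveal this.

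The size is about 0.036 Rankin points and 0.006 EQ-5D units per death in an arm of 140. This rests on assumed baselines of 1 and 0.8 and on scoring death as 6 and 0. With equal mortality the between-arm effect is nil, and with an assumed gap of 2 to 3 percentage points it is 0.014 to 0.024 EQ-5D units. The total cannot be settled from the article because it gives no death rate. The primary outcome is essentially unaffected, and the sample size and power do not change.

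**What to change.** Replace the general rule in Statistical analysis with text such as:

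> Baseline observation carried forward applies to the six-month BP and lipid outcomes only, and only in patients not known to have died. A known death is not missing data. From the date of death the EQ-5D index is 0 and the modified Rankin score is 6, its worst category. As a sensitivity analysis, EQ-5D and Rankin results in survivors are shown beside mortality in each arm.

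One clause should say how deaths enter the BP and lipid analyses. Counting them as non-attainers keeps the target outcomes essentially as they are, and the continuous changes need an explicit choice. Analysing the Rankin scale as ordinal fits this scoring but is optional. If the cost-effectiveness analysis uses EQ-5D, the same scoring should carry through to it.

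The cost is a few sentences. Vital status is already collected, so no new data are needed and the sample size does not change. The small downside is slightly more variable EQ-5D and Rankin means.
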